#### Secondary outcomes

The secondary outcomes are smoking, craving, mood and mindfulness as measured by experience sampling. Smoking will be measured using the Tracker. Craving will be measured using the check-in question "When you started this check-in, how much were you craving a cigarette?" Prediction of smoking by craving will be tested using standard regression analyses with group and craving as independent variables and smoking as the dependent variable [15]. Formal (meditation) and informal (RAIN) practice will be included in the model as independent predictor variables [15] to test whether meditation practice during treatment moderates the change in the prediction of smoking by craving across study time points.

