### Retention strategies

Treatment retention will be defined as completing 75% of mobile mindfulness training modules. Retention rates will be ensured by: (i) emphasizing the importance of follow-up at study initiation and through follow-up; (ii) requesting three referrals at study initiation who can update a participants’ contact information; (iii) paying $10 for the end of treatment survey, $20 each for surveys at 3- and 6-months follow-up, and $0.50 per experience sampling "check-in" [24]; and (iv) paying for participation (up to $116 total) at 6-months follow-up. All randomized participants will be followed up and their true smoking status used in the analysis, and follow-up will be collected blind to group allocation [30].

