Experience sampling is embedded in the app as “check-ins.” Based on previous experience sampling methods for smoking cessation [33], participants will be prompted six times per day to check-in, each day of the 22-day program. They will set the daily start and end times for check-ins, their day will be divided into six intervals, and they will be prompted to check-in at a random time in each interval [23]. Each check-in will ask the following questions adapted from the Day Reconstruction Method [34] and from prior studies using experience sampling [23,24]: (1) When you started this check-in, what were you doing? Categorical response (traveling, working, eating, internet/texting, relaxing, reading, talking, grooming, housework, watching TV, shopping/errands, caring for children, preparing food/eating, exercising, other). (2) When you started this check-in, how aware were you of what you were doing? Visual analog scale (VAS) from not at all to very much. (3) When you started this check-in, how distracted or focused were you? VAS from very distracted to very focused. (4) When you started this check-in, how was your experience feeling? VAS from very unpleasant to very pleasant. (5) When you started this check-in, how were you relating to your experience? VAS from really wanted it to stop to really wanted it to continue. (6) When you started this check-in, how much were you craving a cigarette? VAS from not at all to very much. (7) When you started this check-in, how much were you feeling these emotions? VAS from not at all to extremely, for each: relaxed, anxious, joyful, tired, content, sad, excited, irritable. (8) The tracker says you have smoked (#) cigarettes today. Adjust your tracker below if needed. Today I have smoked: (#). Participants will be sent a reminder text message if their response rate drops below 3 check-ins in 24 hours. Any day with less than 3 completed check-ins will be excluded from the analysis. Based on prior studies [23] a response rate of 80% is expected.

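### Standard regression is named for repeated experience-sampling data with no unit of analysis and no allowance for within-person correlation

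*Protocol article*

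**What the plan says.** The Secondary outcomes section of the protocol article gives the data source: "The secondary outcomes are smoking, craving, mood and mindfulness as measured by experience sampling". Smoking is taken from the Tracker and craving from one check-in item. The method follows: "Prediction of smoking by craving will be tested using standard regression analyses". Smoking is the outcome, and group and craving are the predictors. Meditation and RAIN use are added as further predictors, to see whether practice alters how the craving–smoking relation changes over the study's time points.

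The Intervention group section sets the sampling: "participants will be prompted six times per day to check-in, each day of the 22-day program". It adds that "a response rate of 80% is expected" and gives a day-level rule: "Any day with less than 3 completed check-ins will be excluded from the analysis". The last check-in item shows the day's count so far for correction: "The tracker says you have smoked (#) cigarettes today". The Control group section matches these procedures.

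The article does not say whether a row of the regression is a check-in, a day or a participant. It names no random effect, clustered variance or aggregation step.

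**The concern.** Ordinary regression assumes independent errors. Records from one smoker share that smoker's usual consumption, usual craving and possibly their own craving–smoking slope, while group differs only between people. If many rows per person enter as though independent, the standard error for group is too small. Those for craving and group-by-craving may be too small as well.

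At stake is the article's only stated secondary aim, that mindfulness training weakens the link between craving and smoking. A falsely precise test could support that mechanism by chance.

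There is a linked question about the outcome. The count shown at each check-in accumulates over the day. If it were regressed on craving at the same check-in, craving would be related to cigarettes already smoked, which is not prediction.

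**Working it through.** **1. Records per participant.** Six prompts × 22 days = 132. The payment terms in Retention strategies confirm this. The components are "paying $10 for the end of treatment survey, $20 each for surveys at 3- and 6-months follow-up, and $0.50 per experience sampling" check-in, and the ceiling is "paying for participation (up to $116 total) at 6-months follow-up". Then 132 × $0.50 + $10 + $20 + $20 = $66 + $50 = $116, an exact match. At the expected 80% response, 0.80 × 132 = 105.6, or about 106 check-ins. Day-level rows number at most 22.

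**2. The group term.** For a predictor that is constant within a person, with m rows each and exchangeable within-person correlation (ICC):

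- design effect DE = 1 + (m − 1) × ICC
- actual error of a nominal 5% test = 2 × [1 − Φ(1.96 / √DE)]

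Example with m = 106 and ICC = 0.1: DE = 1 + 105 × 0.1 = 11.5, √DE = 3.39, 1.96 / 3.39 = 0.578, giving an error rate of 0.56. The article gives no ICC, so every value below is an assumption.

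| Assumed ICC | DE, m = 106 | Actual error | DE, m = 22 | Actual error |
|---|---|---|---|---|
| 0.01 | 2.0 | 0.17 | 1.2 | 0.075 |
| 0.05 | 6.2 | 0.43 | 2.0 | 0.17 |
| 0.1 | 11.5 | 0.56 | 3.1 | 0.27 |
| 0.3 | 32.5 | 0.73 | 7.3 | 0.47 |
| 0.5 | 53.5 | 0.79 | 11.5 | 0.56 |

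**3. The craving and group-by-craving terms.** The formula above does not cover these, so they were simulated under the null. The simulation used 118 participants (59 per group, from the Sample size section), 106 rows each, a normal outcome, and 600 runs per setting. Ordinary least squares on individual rows gave these rejection rates at a nominal 5%:

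| ICC of smoking | ICC of craving | SD of person-specific slope | Group | Craving | Group × craving |
|---|---|---|---|---|---|
| 0.3 | 0 | 0 | 0.74 | 0.045 | 0.06 |
| 0.1 | 0.1 | 0 | 0.55 | 0.18 | 0.18 |
| 0.1 | 0.1 | 0.1 | 0.54 | 0.27 | 0.27 |
| 0.3 | 0.3 | 0 | 0.72 | 0.56 | 0.49 |
| 0.3 | 0.3 | 0.2 | 0.73 | 0.59 | 0.58 |
| 0.5 | 0.5 | 0 | 0.79 | 0.72 | 0.71 |

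The first line shows no inflation of the craving terms when craving varies only within people and slopes do not differ. The rest show that inflation grows with between-person variation.

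**4. Do the remedies work?** In the same simulations, participant-clustered standard errors, and separately one mean per participant, gave about 0.03 to 0.07 for all three terms. That is nominal within simulation error: the standard error of an estimated 0.05 from 600 runs is √(0.05 × 0.95 / 600) = 0.009.

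**5. The smoking outcome.** The check-in count is a running daily total. The Secondary outcomes section names the Tracker as the source but gives no interval over which cigarettes are counted and no ordering relative to the craving rating. A same-check-in regression is therefore neither specified nor excluded.

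**The case against.** The strongest reply is that the article never says a row is a check-in. The figure of 132 belongs to the sampling schedule, not to the model. The Sample size section supports this aim with an earlier sample of 33, at baseline and at end of treatment, which counts people rather than records. With one value per participant there is no inflation. The article also condenses a fuller plan, where the unit of analysis may be set out.

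Much of this stands. A reader might infer that the plan does fit ordinary regression to 132 records per person, so that its p-values are bound to be far too small. The text does not support that. The unit is open, and even with repeated rows the craving terms need not be inflated. Nor does the text show that the running total will be regressed on craving at the same check-in. The Tracker is a separate feature of the app, and daily totals fit the wording equally well.

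Two things count the other way. First, the article does more than stay silent: it names a method that assumes independence, for data collected repeatedly within people. Second, its own text leans towards several rows per person. The exclusion rule works on days, and testing a change over time in one model needs at least two rows per person unless change scores are used, which are not mentioned. Separate regressions at each time point would not formally test a change.

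**Conclusion.** The concern holds in conditional form. The method as named neither fixes the unit of analysis nor handles within-person correlation.

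- If rows are check-ins or days, the group test is anti-conservative: about 56–79% false rejection with 106 check-in rows and 27–56% with 22 day rows, for assumed ICCs of 0.1 to 0.5. With check-in rows, even an ICC of 0.01 gives about 17%.
- For craving and group-by-craving with check-in rows, the simulated range runs from none (about 5–6%) to about 70%, depending on assumed between-person variation in craving and its slope.
- If each participant contributes one value, there is no inflation.

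These sizes rest on assumed ICCs and slope variances, exchangeable correlation and a normal outcome, none of which the article supplies. The ordering of smoking and craving is a matter to be defined, not a demonstrated error. The primary comparison of abstinence at 6 months uses one outcome per person and is untouched. Severity is moderate.

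**What to change.** State the unit of analysis and replace the standard-regression wording with one of the following:

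- a mixed model with a participant random intercept and a random craving slope;
- GEE with participant-clustered robust standard errors;
- explicit participant-level summaries analysed by ordinary regression, with the change over time points expressed so that each person contributes one value.

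Also define the smoking outcome as cigarettes logged over a stated interval that follows the craving rating, so that the Tracker's running daily total is not regressed on craving at the same check-in.

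The cost is a wording change, slightly more modelling work and wider reported intervals. No change to data collection or the primary analysis is needed.

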This trial is innovative by: (i) mobile mindfulness training merges a new treatment for smoking –mindfulness training –with a novel delivery method –smartphone app; (ii) mobile mindfulness training can potentially improve efficacy by bringing mindfulness into real-world contexts; (iii) experience sampling will capture real time, real-world smoking, craving, mood, and mindfulness, by smartphone app, whereas prior studies were limited to text messaging or web-based tools [23-26]; and (iv) a novel comparison group, experience sampling-only, will be used to disentangle the efficacy of mindfulness training from that of effective self-monitoring.

The primary aim is to evaluate the efficacy of mobile mindfulness training plus experience sampling to improve smoking cessation rates at 6-months follow-up as compared to experience sampling-only. It is hypothesized that mobile mindfulness training will contribute to a significantly higher smoking cessation rate at 6-months follow-up as compared to control. The secondary aim is to test the hypothesis that mobile mindfulness training moderates the decoupling of craving and smoking. It is hypothesized that mobile mindfulness training will moderate the change in the prediction of smoking by craving across study time points. It is also hypothesized that meditation practice during treatment will moderate this change.

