### Sample size

The sample size was determined based on the prior study of in-person mindfulness training for smoking cessation [14]. Cell size was determined by a *χ*^*2*^ power analysis using one-week point prevalence abstinence at end of treatment and at 4-months follow-up from that study. Point prevalence abstinence differed between groups by 20% or more at each time point. Thus it is estimated that group sizes of 59 per group will achieve 80% power to detect a 20% group difference at *p* < .05 using a two-sided *Z*-test with pooled variance. 140 subjects will be recruited to allow for 12-15% attrition. Further, a sample size of 33 was sufficient to detect a significant prediction of smoking by craving at baseline and significant effects of meditation on smoking at end of treatment [15], therefore these group sizes will be sufficient to detect similar changes.

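### The practice terms named as a test of moderation are main effects that leave the craving slope unchanged, and no test is named for moderation by group

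*Protocol article*

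**What the plan says.** The last paragraph of the Background in the protocol article sets out the secondary aim as two hypotheses. On training: "It is hypothesized that mobile mindfulness training will moderate the change in the prediction of smoking by craving across study time points". On practice: "It is also hypothesized that meditation practice during treatment will moderate this change".

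The Secondary outcomes section gives the analysis in two sentences.

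- The first concerns whether craving predicts smoking, and specifies "standard regression analyses with group and craving as independent variables and smoking as the dependent variable".
- The second adds practice: "Formal (meditation) and informal (RAIN) practice will be included in the model as independent predictor variables". Its stated purpose is "to test whether meditation practice during treatment moderates the change in the prediction of smoking by craving across study time points".

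Both sentences cite an analysis from the earlier in-person trial. No product term, time term or comparison of slopes between arms is named anywhere in the article.

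The Sample size section supports this aim by noting that "a sample size of 33 was sufficient to detect a significant prediction of smoking by craving at baseline". It adds that the same number sufficed for effects of meditation on smoking at the end of treatment.

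**The concern.** Moderation here means that the slope of smoking on craving differs by arm or by amount of practice. The hypotheses go one step further and concern how that slope changes over time. A regression that holds group, craving and practice only as separate predictors has one slope for everyone, so none of its coefficients answers either question.

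The error could run in both directions. If training weakened the link between craving and smoking without altering the average amount smoked, the group and practice coefficients would have no reason to move. If the app simply reduced smoking, which is its purpose, those coefficients could be significant with no decoupling at all. Because the practice sentence labels its terms as a test of moderation, such a result could be reported as decoupling. The Discussion presents the craving-smoking association as one of the outcomes on which the app is to be judged against in-person training, so the point bears on a stated claim of the trial.

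**Working it through.** **Inputs.** The hypotheses come from the Background and the model terms from Secondary outcomes. The figure of 59 per group comes from Sample size. The plan gives no figure for this analysis, so there is none to reproduce.

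**1. The model as written.** Let S be smoking, G group, C craving, F formal practice and R RAIN practice:

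E[S] = b0 + b1·G + b2·C + b3·F + b4·R

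The craving slope is dE[S]/dC = b2, whatever the values of G, F and R. The coefficients b1, b3 and b4 are differences in the amount smoked at a fixed level of craving.

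**2. What the training hypothesis needs.** With time T:

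E[S] = b0 + b1·G + b2·C + b3·T + b4·GC + b5·GT + b6·CT + b7·GCT

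- Craving slope: b2 + b4·G + b6·T + b7·GT
- Change in that slope per unit of time: b6 + b7·G
- Difference between arms in that change: b7

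The hypothesis is about b7. The stated model amounts to b4 = b6 = b7 = 0.

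**3. What the practice hypothesis needs.** Within the intervention arm, with P for practice, the slope is c1 + c2·P + c3·T + c4·PT. Its change per unit of time is c3 + c4·P, and the test is of c4. The stated model contains neither c2 nor c4. Practice is taught only in the intervention arm (Intervention and comparator), so in a pooled model it is also largely confounded with group.

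**4. Would separate fits at each time point help?** They would let b2 vary over time, but each fit would still force one slope across arms and practice levels. The change in slope would be common to everyone.

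**5. Illustration with assumed values.** One record per person, 59 per group, standardised craving centred at zero, residual SD 1, two-sided 0.05, 4000 replicates.

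| True state | Group coefficient, additive model | Group x craving term |
|---|---|---|
| Slopes 0.5 (control) v 0, no group main effect | 5.0% reject | 75% reject |
| Equal slopes, group main effect -0.5 | 77% reject | 5.1% reject |

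Hand check: the standard error of either contrast is about √(2/59) = 0.184. Then 0.5/0.184 = 2.72, and power is about Φ(2.72 - 1.96) = Φ(0.76), or roughly 78%. This is close to the simulated 75% and 77%.

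The 5.0% follows from assuming that both arms smoke the same amount at average craving. A variant with repeated days looked at practice: 59 per arm, 20 days each, person SD 4 and residual SD 3 cigarettes, craving slope 1 - 0.5 x practice, practice mean 1 and SD 0.5 in the intervention arm and 0 in control. The practice main effect rejected in 6% to 8% of runs and practice x craving in 44% to 45%.

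Both set-ups hold the slopes constant over time. They show which term responds to moderation, and do not give the power for the hypothesised change over time.

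**The case against.** The strongest reply is that the article lists the variables in the model rather than its full set of terms. It nowhere says main effects only. The word independent can be read as the counterpart of dependent, and a sentence whose purpose is to test moderation points towards an interaction. Both sentences cite an earlier analysis, and the Background reports that in that trial home practice weakened the association between craving and smoking, which is a moderation result. That analysis and the full analysis plan may contain the product terms.

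Several parts of this stand.

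- A reader might infer that the plan excludes interactions. The text does not say so; it names none.
- A reader might infer that the group and craving sentence is itself put forward as a test of moderation by group. It claims only to test whether craving predicts smoking. For training, the article is silent on the test; for practice, it ties the wrong terms to the purpose.
- A reader might infer that only product terms could repair the analysis. For the group hypothesis, arm-specific fits with a formal comparison of the change in slope would also serve.
- A reader might take the simulated percentages as the size of the loss in this trial. They rest on assumed values and have no time dimension.

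What does not stand is that this is merely detail left to a fuller document. The practice sentence commits to particular terms and says what they are for, and those terms do not do that job. An analysis plan that followed the wording would carry the mismatch forward.

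**Conclusion.** The point holds in limited form. The article ties the practice main effects to a test of moderation that they cannot provide, and it names no test for the hypothesis that training moderates the change in the craving slope. This rests on reading the model as written and on algebra alone; no assumed value is needed. How much power would be lost, or how often a plain fall in smoking would be mistaken for decoupling, cannot be stated from the document.

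It would be too strong to conclude that the secondary aim will certainly go untested, because product terms are not ruled out and the cited analysis is not shown. The primary chi-square comparison of abstinence is untouched and no data collection is affected. The severity is moderate: it should be fixed, preferably before outcome data are examined, so that the moderation tests are prespecified.

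**What to change.** Restate the secondary analysis in Secondary outcomes as follows.

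- Training: the test is the group x craving x time coefficient, or an equivalent formal comparison between arms of the change in craving slope, with all lower-order terms in the model.
- Practice: the test is the practice x craving x time coefficient, for formal and for RAIN practice, estimated within the intervention arm and with all lower-order terms.
- Add that the main effects of group and of practice describe the amount smoked and are not tests of moderation.

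If interactions were intended all along, this only makes them explicit. The cost is a sentence or two and no new data. The downside is that interactions are estimated less precisely than main effects. The Sample size remark about 33 participants concerns the craving prediction and meditation effects on smoking, not an interaction, so it gives no assurance of power for these tests. The report should say so and give confidence intervals for the interaction coefficients.

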#### Exploratory outcomes

Theory-based potential mechanisms will be tested using mediation analyses of variables related to smoking, craving, mood and mindfulness, and other psychological variables, evaluated using 15-minute online surveys at baseline, 1-, 3-, and 6-months from treatment initiation, including: (i) smoking demographics, including self report of smoking abstinence over the follow-up period allowing up to five cigarettes total [30]; (ii) 4-item Alcohol Use Disorders Identification Test (AUDIT-C; [38]); (iii) 15-item Minnesota Nicotine Withdrawal Scale-revised (MNWS-R; [39]) to evaluate nicotine withdrawal symptoms (i.e., craving, irritability, anxiety, depression, difficulty concentrating, appetite, insomnia, restlessness, impatience, constipation, dizziness, coughing, dreaming/nightmares, nausea, sore throat); (iv) 4-item Perceived Stress Scale (PSS; [40]) to measure the degree to which situations in one's life are appraised as stressful over the last week; (v) 12-item Smoking Self Efficacy Questionnaire (SEQ; [41]) to evaluate the self-efficacy to resist the urge to smoke; (vi) 24-item Five Facet Mindfulness Questionnaire short form (FFMQ-SF; [42,43]) to measure mindfulness related to observing, describing, acting with awareness, non-judging of inner experience, and non-reactivity to inner experience; (vii) 12-item Self Compassion Scale short form (SCS-SF; [44,45]) to evaluate how one typically acts toward oneself in difficult times; (viii) 22-item Craving Experience Questionnaire (CEQ; [46]) to measure desire and craving to smoke; (ix) exercise, eating, and relaxation methods questions, including prior meditation experiences; and (x) 6-item Gratitude Questionnaire (GQ-6;500 [47]) to evaluate one's proneness to experience gratitude in everyday life. Participants will be paid $10 for the 1-month survey, and $20 for each 3- and 6-months survey, the total to be paid at 6-months.

